#### Data collection

A field enumerator using ODK and the wayfinding app Maps.me will visit each selected housing structure. The geolocation of each housing structure will be recorded in ODK. If the house is inhabited, the study will be explained in lay terms to the present household members and they will be invited to participate in the survey. Information and consent forms (ICF) for all eligible household members and assent forms for children aged 12 to 18 years will be distributed. Once adult participants and in the case of children aged below 18 years their parents provided written informed consent by signing the form and, additionally, once children aged 12 to 18 years agreed to participate by signing the child assent form, plastic containers (100 ml) for urine collection will be distributed for each participant. The plastic containers will be labelled with a unique identifier code and an individual sticker picture, which both match the same identifier code and sticker picture on a provided paper form containing the household member names to support their correct identification. Additionally, one adult household member will be invited to answer several questions related to participation in the last MDA, water contact behaviour, access to safe water sources, opinion regarding intervention approaches against schistosomiasis, and the number of individuals living in the household and their main demographic information, such as sex and age. On the following day, the study team will revisit the households and collect the (remaining) signed ICFs, signed assent forms and filled urine containers. Each shehia will be visited for three days, to cover all selected houses and ensure maximal participation and compliance with urine collection.

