### Annual community-based parasitological surveys

#### Selection of houses and participants

For the annual community-based surveys, 70 housing structures per shehia will be selected by a computer-based randomisation procedure from Geographical Information System (GIS) shape files provided by the Zanzibar Mapping Initiative (http://www.zanzibarmapping.com) of the Commission of Lands Zanzibar. Randomly selected housing structures will be located by field enumerators by using the navigation app Maps.me (https://www.maps.me/) combined with ODK installed on a computer tablet (Samsung Galaxy Tab A 2019). Accounting for a 30% dropout of housing structures that may not be inhabited (i.e. shops, sheds, mosques, houses under construction or abandoned houses) and households without any member willing to participate, we estimate that we will have a final sample size of 50 houses per shehia included in the survey. People sharing the same kitchen or pot will define a household. All household members meeting the inclusion criteria will be invited to participate in the survey and to provide one own urine sample, which will be examined for *S. haematobium* infection markers. With an average of five people per household, we estimate to collect urine samples from a total of 250 participants per shehia. Additionally, one adult household member present at the first visit to the house will be invited to participate in a questionnaire survey to assess household characteristics. If more than one adult is present and eligible to participate at first visit, we will randomly select the participant of the questionnaire survey by using a playing-cards approach.

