#### Intervention packages and data collection in hotspot implementation units

In the hotspot IUs, where a considerable part of the population is still infected with *S. haematobium*, we will implement a multi-disciplinary intervention package including MDA, snail control and behaviour change communication activities.

Large-scale MDA with praziquantel is the corner stone for the control and prevention of morbidity due to schistosomiasis [3, 5]. Praziquantel treatment is administered without prior diagnosis to large parts of the population living in endemic areas. In our hotspot IUs, MDA will be conducted at least annually in communities and schools by the Zanzibar NTD Programme. In communities, community drug distributors trained by the MoHSWEGC will visit all households in a door-to-door approach and offer to treat children aged 4 years or older with praziquantel (40 mg/kg) if they do not receive treatment in schools. Moreover, they will offer praziquantel to all adults that are eligible for treatment according to national treatment guidelines. In schools, praziquantel (40 mg/kg) will be provided to all children present at the day of treatment by teachers and staff of the Zanzibar NTD Programme using a dose pole [50]. The intake of tablets will be directly observed. Treatment coverage will be reported by the Zanzibar MoHSWEGC based on reports from their staff, community drug distributors, and teachers. Moreover, we will conduct our own post-treatment coverage surveys in line with the annual cross-sectional parasitology surveys in the hotspot communities and schools. When invited to submit a urine sample for annual monitoring, individuals enrolled in the survey will also be invited to respond to an ODK questionnaire, asking if they have received and swallowed the drugs provided in the MDA treatment round preceding the survey.

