### Statistical methods

To analyse the primary outcome, we define the sensitivity of the surveillance system as the proportion of cases detected:$${\text{SE}} = {\text{N}}_{{{\text{inf detected by surveillance}}}} / {\text{N}}_{{{\text{inf}}}}$$

The total number of infected persons is unknown but will be estimated from the cross-sectional surveys as:$${\text{N}}_{{{\text{inf}}}} = {\text{ P}}_{{{\text{school}}}} *{\text{ N}}_{{{\text{school}}}} + {\text{ P}}_{{{\text{non}} - {\text{school}}}} *{\text{ N}}_{{ {\text{non}} - {\text{school}}}}$$whereby prevalences (P) and corresponding confidence intervals are estimated via generalized estimating equations for binary data with independent correlation structure to account for correlation within clusters.

The prevalence and intensity of *S. haematobium* infections will be calculated by different diagnostic approaches used in the annual cross-sectional surveys. Intensity of infection will be classified into light (< 50 eggs/10 ml urine) and heavy (≥ 50 eggs/10 ml urine) according to thresholds provided by the WHO for urine filtration results [3].

The timeliness of case notification and reactive intervention will be assessed by recording the time needed from diagnosis to treatment, from diagnosis to follow-up of *S. haematobium* positive individuals and test-and-treat of their household members, and from diagnosis to reactive snail control.

The acceptability of the surveillance-response approach will be assessed by a mixed methods approach based on the results of questionnaires run in parallel to test-and-treat approaches in low-prevalence shehias.

The coverage of test-and-treat activities will be calculated by assessing the number of people who were targeted by test-and-treat activities in relation to the total population.

MDA coverage will be calculated by assessing the number of people reporting in the cross-sectional surveys that they received praziquantel during the last MDA in relation to the total number of participants in the cross-sectional surveys.

MDA compliance in hotspot areas will be calculated by assessing the number of people reporting in the cross-sectional surveys that they have taken praziquantel as recommended, in relation to the total number of participants in the cross-sectional surveys.

The impact of snail control will be determined by assessing the snail abundance and number of intermediate host snails at each HWCS identified over time during regular snail surveys.

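### The protocol names two different respondents for the last-MDA question in the community survey, and the all-participants denominator for coverage and compliance fits only one of them

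*Protocol article*

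**What the plan says.** Four places in the protocol article bear on how MDA uptake is measured.

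- **Annual community-based parasitological surveys, Selection of houses and participants.** All eligible household members are invited to give urine. Separately, "one adult household member present at the first visit to the house will be invited to participate in a questionnaire survey", chosen at random if several adults are at home. The stated purpose of that questionnaire is household characteristics.
- **Same survey, Data collection.** "one adult household member will be invited to answer several questions related to participation in the last MDA", along with water contact, safe water, opinions on interventions, household size and members' demographics. For the other members this section lists only consent or assent and urine collection.
- **Intervention packages and data collection in hotspot implementation units.** The study runs its own coverage survey "in line with the annual cross-sectional parasitology surveys in the hotspot communities and schools". At the urine invitation, "individuals enrolled in the survey will also be invited to respond to an ODK questionnaire, asking if they have received and swallowed the drugs".
- **Statistical methods.** The coverage numerator is the "number of people reporting in the cross-sectional surveys that they received praziquantel during the last MDA". The denominator is everyone who took part in the cross-sectional surveys. Compliance has the same denominator. The compliance sentence names hotspot areas; the coverage sentence does not.

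For comparison, Data collection under School-based parasitological surveys records participation in the last MDA round for each registered child.

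**The concern.** The two community descriptions differ on the respondent: one adult per household, or each enrolled individual. The formula in Statistical methods is right for the second. Under the first it can count people who were never asked as people who did not receive the drug.

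MDA coverage in hotspot areas is a stated secondary outcome (Primary and secondary objectives), and compliance is built the same way. The Discussion treats good coverage as essential to the intervention approach, so the prevalence seen in hotspots is hard to interpret without a sound coverage figure.

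Door-to-door delivery also reaches children aged 4 years or older who are not treated at school. Study setting gives net primary enrolment of 68.4% in Micheweni and 81.9% in Wete (2014/15), so children outside primary school are not a negligible group. If only one adult per house is asked, and only about him- or herself, nobody reports for them.

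**Working it through.** **Inputs.** Per shehia, from Selection of houses and participants (community survey): 70 structures, 30% loss, 50 houses, five people per household, 250 participants. From the school survey: 140 children per school. From Sample size: 7,800 individuals a year over 20 shehias.

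**Reproducing the plan's figures.**
- Houses: 70 × (1 − 0.30) = 49, stated as 50 (rounding).
- Community participants: 50 × 5 = 250, as stated.
- Yearly total: 20 × (140 + 250) = 7,800, as stated.

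The protocol gives no coverage figure, so there is none to reproduce.

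**Ceiling.** Highest attainable coverage = persons asked / participants in the denominator.

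*Each enrolled person is asked (hotspot section).* 250/250 = 100%. True coverage c is returned as c. The same holds if the one adult reports for every member.

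*One adult per household, self-report only, all participants in the denominator.* 50/250 = 20%. Participants per household is the only driver. Taking 3 to 7 as an assumed range:

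| Participants per household | Ceiling, community |
|---|---|
| 3 | 50/150 = 33.3% |
| 4 | 50/200 = 25.0% |
| 5 (plan) | 50/250 = 20.0% |
| 6 | 50/300 = 16.7% |
| 7 | 50/350 = 14.3% |

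For assumed true coverage of 60%, 75% or 90%, with the adults asked covered at the same rate as everyone else, the community figure would be 0.60 × 50/250 = 12%, 0.75 × 50/250 = 15% or 0.90 × 50/250 = 18%.

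*Pooled with schools.* Every schoolchild is asked, so the ceiling is (50 + 140)/(250 + 140) = 190/390 = 48.7%. The same true values would read 29.2%, 36.5% and 43.8%. The protocol does not say that the two samples will be pooled for coverage, nor that they will be kept apart.

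**Would a denominator change alone be enough?** Limiting the denominator to persons asked removes the ceiling, but under the one-adult procedure the community estimate then describes adults at home at the first visit. It would also be less precise. At an assumed coverage of 75%, ignoring clustering, the 95% half-width per shehia is 1.96 × √(0.75 × 0.25/50) = 12.0 percentage points with 50 respondents, against 1.96 × √(0.75 × 0.25/250) = 5.4 with 250.

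**The case against.** The strongest reply is that the two descriptions can coexist. The hotspot section is the one that sets out coverage measurement, and its wording allows an individual question in hotspots on top of a general household interview in all 20 shehias. On that reading the denominator matches the people asked and the formula is correct. The selected adult is also already an informant for the household, since he or she gives its size and its members' sex and age, and may report MDA uptake for them too. The handling of unanswered items is commonly left to an analysis plan, which is not shown. Coverage is also reported by the Ministry from its staff, drug distributors and teachers, so an implausibly low survey figure would probably be noticed.

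Much of this stands. A reader might infer that coverage will be capped at 20%, that good delivery will be reported as failure, or that out-of-school children are not measured. The document does not support any of these as a settled result: under the hotspot section there is no cap, and enrolled community members aged 4 years or older are asked.

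The reply does not remove the conflict. The community procedure describes no individual interview for members other than the selected adult, whereas the school procedure does so for every child. It does not say that the adult answers for others on MDA. An analysis plan can choose a denominator, but it cannot supply answers that were not collected.

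**Conclusion.** The point holds as a conflict between stated procedures with a conditional consequence. It is certain that the community survey sections and the hotspot section name different respondents for the MDA question, and that Statistical methods uses all participants as the denominator for both coverage and compliance.

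The community ceiling of about 20% (14% to 33% for an assumed 7 to 3 participants per household) rests on three assumptions together: the one-adult procedure is the one followed in hotspots, the adult answers for self only, and people not asked remain in the denominator. If any one fails, that ceiling does not arise. The absence of any report for children not treated in school rests on the first two. The pooled figure of 48.7% further assumes that school and community samples are combined.

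Two secondary measures are affected. The primary outcome, which concerns surveillance in low-prevalence areas, is not. The matter is worth settling before data collection because the loss could not be repaired afterwards.

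**What to change.** 1. In Selection of houses and participants and in Data collection (community survey), state the respondent in agreement with the hotspot section: in hotspot shehias, record received and swallowed for each enrolled household member, by self-report, or by caregiver proxy for young children. Mark which answers are proxy. If the hotspot questionnaire is meant to be separate from the household interview, say so.
2. In Statistical methods, limit the denominators of coverage and compliance to hotspot participants with an MDA answer, and give the number without one. Name hotspots in the coverage sentence, as the compliance sentence and the objectives already do.
3. Report community and school coverage separately.

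The cost is two fields per person in the household questionnaire, a few minutes per house, and edits to three sections. The drawback is that some answers for young children will be by proxy.

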### School-based parasitological surveys

#### Selection of participants

The annual school-based cross sectional survey will be conducted in the main public primary school of each shehia. If a shehia has several public primary schools, the school with most students will be surveyed. If a shehia has no public primary school, no school will be surveyed. In each of the schools, a total of 175 students aged 4–17 years will be randomly selected for urine collection. For this purpose, one class of each nursery and standard 1–6 grades, will be selected based on computer-randomised lists. In the selected classes, all children will line up, stratified by sex. Subsequently, we will systematically select each third child in the lines to be included in the study until 25 children per class are reached. This procedure will be continued until we reach a total of 175 selected children from the 7 selected grades. Accounting for a 20% drop-out due to non-consenting parents, absenteeism of children or inability to produce a urine sample of sufficient volume, we aim for a final sample size of 20 children per standard (i.e. a total of 140 students per school).

#### Data collection

Each selected child will be provided with an ICF for their parents to read and sign. Each selected child aged 12 years or older will additionally be invited to sign an assent form on its own behalf. On the following day, once signed ICFs and assent forms are submitted, children will be registered, including information about their age, sex, travel history and participation in the last round of MDA. Subsequently, children will be handed over a plastic container labelled with a unique identifier code and invited to produce their own urine sample, which will be collected by the study team on the same morning. In addition, participants from grade 3, 4, and 5 will be invited to participate in a questionnaire interview about the knowledge, attitudes and practices regarding schistosomiasis transmission and prevention (KAP). The children will be asked about their knowledge of the animals that are part of the *S. haematobium* lifecycle, their own water contact behaviour, access to safe water sources, and their knowledge about opportunities to prevent both getting and spreading schistosomiasis.

### Interventions and data collection

In the study, specific intervention packages will be tailored and adapted to the local micro-epidemiology of urogenital schistosomiasis in the shehias. Low-prevalence IUs will receive tailored surveillance-response measures, consisting of active, passive and reactive case finding, treatment of *S. haematobium*-positive individuals and focal snail control. Hotspot IUs will receive a multi-disciplinary intervention package including MDA, snail control and behaviour change communication. The classification of the study shehias into low-prevalence or hotspot IUs will be based on the results of annual cross-section surveys. Initially, a shehia will be considered a low-prevalence IU if it shows an apparent *S. haematobium* prevalence < 2% in the community-based survey and an apparent *S. haematobium* prevalence < 3% in the school-based survey, based on single urine filtration microscopy. Otherwise, the shehia will be considered a “hotspot” IU (Fig. 3). Results gained over the study period will show whether these thresholds and respective intervention packages successfully sustain and accelerate the gains and prevent recrudescence of *S. haematobium* transmission in low-prevalence IUs. The thresholds will be evaluated annually in light of the results of the cross-sectional surveys and adapted if needed.

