**Fig. 1 Fig1:**

Programmatic steps to control and eliminate schistosomiasis. In green and gray text boxes: recommendations according to WHO [4]; in blue fonts and yellow text box: additional components of the SchistoBreak study. PC: preventive chemotherapy; IU: implementation unit

A wealth of experience and insights regarding multi-disciplinary interventions and research for urogenital schistosomiasis elimination was gained over the past decade from 2011 to 2020 within the Zanzibar Elimination of Schistosomiasis Transmission (ZEST) project [6, 16–19]. The islands Pemba and Unguja, belonging to the Zanzibar archipelago of the United Republic of Tanzania, used to be highly endemic for urogenital schistosomiasis in the past century [20–22]. To combat urogenital schistosomiasis, caused by *Schistosoma haematobium*, on the islands, regular MDA campaigns with praziquantel administration to schoolchildren and the whole community were implemented since the 1980s [23–26]. In 2010, Zanzibar had managed to reach low prevalences of *S. haematobium* infections and subsequently committed to eliminate urogenital schistosomiasis from the islands [17, 18]. From 2012 till 2017, in addition to biannual MDA, some randomised areas received interventions with chemical mollusciciding to target *Bulinus globosus,* the intermediate host snail for *S. haematobium* in Zanzibar [27, 28] and behaviour change measures to reduce people`s freshwater contact [17, 19]. In 2017, most areas on the Zanzibar islands had eliminated urogenital schistosomiasis as a public health problem (defined as < 1% heavy intensity infections) [5, 17, 18]. However, transmission of *S. haematobium* infections was not yet interrupted and several challenges were identified on the way towards schistosomiasis elimination.

These challenges included a marked temporal and spatial heterogeneity of *S. haematobium* prevalence across the islands, as well as the application of standard diagnostic tests with insufficient sensitivity to detect light intensity infections [6, 17, 18, 29–32]. While most of the study sites showed continuously low prevalences from 2011/12 to 2020, some “hotspot” areas with consistent or recurring moderate or high prevalences existed [6, 17, 18]. To address this heterogeneity and to sustain and accelerate the gains made towards elimination, there is a need to target and regularly adapt interventions to the local micro-epidemiology [12, 17, 18].

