### Primary and secondary objectives

The primary objective of this study is to quantify the sensitivity of an adaptive surveillance-response approach for its ability to detect *S. haematobium* infected individuals in low-prevalence areas to trigger an appropriate intervention response. The primary outcome variable will be the number of *S. haematobium* infected individuals detected and reported through the surveillance approach divided by the number of positive individuals in the population as extrapolated from the cross-sectional surveys, i.e. the mean sensitivity of the surveillance-response approach determined over 3 years.

Secondary outcome analyses will cover additional performance parameters of the surveillance approach, as defined by WHO [45]. Moreover, we will assess the impact of multi-disciplinary interventions in hotspot areas, as well as the coverage of test-and-treat activities in low-prevalence areas and of MDA in hotspot areas. Other secondary outcomes will include the accuracy of several diagnostic approaches and micro-mapping of characteristics of the study shehias, including the number and location of schools, madrassas (Islamic schools), and health facilities, the number and location of water bodies and the abundance of intermediate host snails of the genus *Bulinus*.

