### Annual cross-sectional parasitological surveys

The annual cross-sectional surveys will be implemented in all 20 communities and their main public primary schools at sub-district shehia level. This micro-mapping approach will allow us to determine *S. haematobium* prevalences in the school-aged population, which is at highest risk of schistosomiasis, as well as in the whole community to get an accurate picture of infection levels in preschool-aged children, school-aged children, adolescents and adults. The cross-sectional surveys will serve to stratify the study area into low-prevalence and hotspot IUs and hence to micro-target the interventions according to pre-set prevalence thresholds. Moreover, the cross-sectional surveys will allow to determine and monitor the performance of the surveillance-response approach and impact of interventions over the study period. Participants of the annual cross-sectional parasitological surveys identified as infected with *S. haematobium* will be offered treatment with praziquantel (40 mg/kg using a dose pole) [50].

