Third, to control the morbidity due to schistosomiasis, WHO provides several thresholds based on the baseline prevalence among school-aged children to decide upon the treatment strategy and frequency of MDA [3, 4]. However, to our knowledge, with regard to the schistosomiasis elimination goals, official thresholds indicating when to increase the frequency of MDA, or stop large-scale MDA and change tactics to surveillance strategies for detecting elimination or resurgence of transmission are not yet published, but urgently needed. These intervention thresholds for elimination settings should ideally be available for or transferable to a set of different diagnostic methods, which, depending on their sensitivity and specificity, will reveal different prevalences in the same population. Cross-diagnostic threshold adaptation has been evaluated for several standard tests used for the identification of both *S. haematobium* and *S. mansoni*, but only for thresholds at 10% prevalence, with samples from school-aged children, and in settings with higher intensity of infections than in Zanzibar [62, 63]. In our study, the thresholds to stratify low-prevalence IUs and hotspot IUs and the implementation of respective intervention approaches are predicated on single urine filtration results in our cross-sectional surveys and an analytical picture of the micro-epidemiology of urogenital schistosomiasis in Zanzibar established over the past 10 years. Due to age-dependent exposure rates [6, 64], we have initially selected thresholds determining hotspot IUs at ≥ 3% prevalence in individuals aged ≥ 4 years sampled in community-based surveys and at ≥ 2% *S. haematobium* prevalence in schoolchildren sampled in school-based surveys. The suggested thresholds will be subject to change and adaptation over the course of the project, i.e. in case we observe a considerable increase of prevalence in the low-prevalence IUs targeted with surveillance response.

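### The initial 2% and 3% cut-offs that separate low-prevalence from hotspot shehias are swapped between the Methods and the Discussion

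*Protocol article*

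**What the plan says.** **Methods, Interventions and data collection.** The starting rule for a low-prevalence shehia has two conditions, both required: "prevalence < 2% in the community-based survey and an apparent" "prevalence < 3% in the school-based survey, based on single urine filtration microscopy". Every other shehia is a hotspot. The section points to Fig. 3, which is not available here, and says the thresholds will be reviewed each year.

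**Discussion, third challenge.** The initially chosen cut-offs define "hotspot IUs at ≥ 3% prevalence in individuals aged ≥ 4 years sampled in community-based surveys and at ≥ 2" per cent among schoolchildren in the school-based surveys. The same paragraph says the thresholds are "predicated on single urine filtration results in our cross-sectional surveys", and mentions later adaptation only after giving these values.

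**What the class controls.** The Methods state: "Low-prevalence IUs will receive tailored surveillance-response measures, consisting of active, passive and reactive case finding", with treatment of positives and focal snail control. Hotspots receive mass drug administration (MDA), snail control and behaviour change communication. The primary objective (Primary and secondary objectives) concerns detection of "infected individuals in low-prevalence areas to trigger an appropriate intervention response", so the class also fixes which shehias the primary outcome covers.

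**The concern.** The two sections attach the same two numbers to opposite surveys. A shehia whose community or school result falls between 2% and 3% can therefore be low-prevalence under one section and a hotspot under the other.

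Three things are at stake. First, treatment: the class decides whether MDA continues or is replaced by test-and-treat. Second, the primary outcome: the sensitivity of surveillance is estimated over low-prevalence shehias, so a different rule gives a different set of shehias. Third, use of the results: the Discussion stresses that thresholds for stopping large-scale MDA are urgently needed, and a reader looking for the threshold tested here would find two incompatible pairs.

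**Working it through.** **1. Can the two statements be reconciled?**

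| | Methods | Discussion |
|---|---|---|
| Community cut-off | 2% | 3% |
| School cut-off | 3% | 2% |
| Status | initial | initial |
| Diagnostic basis | single urine filtration | single urine filtration |
| Hotspot if | either cut-off reached | not explicit: joined by 'and' |

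Negating the Methods rule gives a hotspot at community ≥ 2% or school ≥ 3%. No reading of the Discussion yields that. Annual adaptation, a different test and mirror-image wording all fail to explain the difference.

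**2. Inputs.** The Sample size section gives 250 community members and 140 schoolchildren per shehia. Check against the stated yearly total: 20 × (250 + 140) = 7800, which agrees.

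**3. Cut-offs as counts.**
- Methods: 2% of 250 = 5.0 and 3% of 140 = 4.2, so low-prevalence means at most 4/250 and at most 4/140.
- Discussion, read as either cut-off sufficing (to match the Methods): 3% of 250 = 7.5 and 2% of 140 = 2.8, so low-prevalence means at most 7/250 and at most 2/140.

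**4. Where the rules disagree (either-cut-off reading).**
- Community 5–7 and school 0–2: hotspot under the Methods, low-prevalence under the Discussion. Example: 6/250 (2.4%) with 1/140 (0.7%).
- Community 0–4 and school 3–4: low-prevalence under the Methods, hotspot under the Discussion. Example: 2/250 (0.8%) with 3/140 (2.1%).

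**5. How often this would happen.** The protocol gives no prevalence distribution across shehias, so the true prevalences below are assumptions. Let X ~ Bin(250, p_c) and Y ~ Bin(140, p_s), independent. Then

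P(disagree) = P(5 ≤ X ≤ 7)·P(Y ≤ 2) + P(X ≤ 4)·P(3 ≤ Y ≤ 4).

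At p_c = 1% and p_s = 1.5%: 0.1038 × 0.6494 + 0.8922 × 0.2899 = 0.0674 + 0.2586 = 0.326. The probability of being low-prevalence is 0.838 under the Methods and 0.647 under the Discussion.

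If 'and' in the Discussion is taken literally, a hotspot needs X ≥ 8 and Y ≥ 3. Every disagreement then runs one way: hotspot under the Methods, low-prevalence under the Discussion.

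| Assumed true community / school prevalence | Either cut-off | Either cut-off, design effect 2 (assumed, beta-binomial) | Literal 'and' |
|---|---|---|---|
| 0.2% / 0.3% | 0.9% | 4% | 0.02% |
| 0.5% / 0.75% | 9% | 13% | 1% |
| 1% / 1.5% | 33% | 27% | 16% |
| 1.5% / 2% | 39% | 30% | 40% |
| 2% / 3% | 26% | 24% | 64% |
| 3% / 5% | 2.8% | 7% | 52% |
| 4% / 6% | 0.3% | 2% | 22% |

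**The case against.** The strongest reply is that only the Methods contain an operative rule. It is complete and refers to the classification figure. The Discussion is a recap that does not say whether one cut-off or both are needed, so nobody could classify a shehia from it without adding an interpretation. If staff follow the Methods, the realised harm is misreporting rather than misallocation. This is plausible, and nothing in the protocol shows that anyone would classify from the Discussion. It does not remove the contradiction, which concerns the rule that assigns treatment and defines the primary-outcome areas.

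A second point is that the probabilities measure how often two rules would disagree if both were applied, at assumed prevalences. They are not misclassification rates. They also do not cover shehias without a public primary school, where no school survey takes place. Both points stand: the figures are illustrative, and the finding does not depend on them.

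A third point concerns which pair is right. The Discussion justifies the pair by age-dependent exposure, and the Annual cross-sectional parasitological surveys section refers to the "school-aged population, which is at highest risk of schistosomiasis". That fits a higher school cut-off, because more infection is expected there. It could also fit a lower school cut-off as a more sensitive trigger. The text alone does not settle it. Fig. 3 might, but even then the two sections would still disagree with each other.

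**Conclusion.** The contradiction holds and needs correcting. The initial 2% and 3% cut-offs are exchanged between the community and school surveys, and no reading of the text reconciles the two statements.

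On the either-cut-off reading, disagreement is confined to shehias with a community or school result from 2% to below 3%. The chance per shehia is between 0.3% and about 39% over the assumed prevalences, or 2% to 30% with an assumed design effect of 2. On the literal 'and' reading it ranges from 0.02% to 64%. The protocol gives no prevalence distribution and describes "a marked temporal and spatial heterogeneity of" infection across the islands, so the number of shehias affected cannot be stated.

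The Discussion is probably the slip: the Methods hold the operative rule, and a higher school cut-off fits the higher risk in school-aged children. This is an inference for the sponsor to confirm.

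**What to change.** Confirm the approved pair, probably that in the Methods. If so, reword the Discussion so that a hotspot is a shehia with at least 2% in the community-based survey **or** at least 3% in the school-based survey. If the Discussion pair is the approved one, correct the Methods instead. In either case use the same and/or logic in both places, check that Fig. 3 shows the same pair, and use that pair to define the shehias in the primary analysis.

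The cost is a wording correction or erratum, with no extra data and no change to sampling.
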